### Estimation of sample size

The primary outcome in this study is the time point of occurrence of chemotherapy-induced hair loss reaching grade II measured by the WHO Toxicity Grading Scale for Determining the Severity of Adverse Events. Our previous results showed that YH0618 could cause the incidence of hair loss grade < II to reach 50% for patients who have completed chemotherapy, and the difference between the incidence of hair loss grade < II in YH0618 group and the control group was 15%. Thus, the difference in proportion between the two groups will be measured by a Z test. To achieve a two-sided, type-I error alpha = 0.05 and power: (1 − beta) = 80%, the minimal number of subject need in each group is 85. We estimated a 20% attrition rate at the end of follow-up; hence, a sample size of at least 107 in each group (214 in total) is planned for this study.

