## Background

Chemotherapy is a major type of cancer treatment using chemical medications to affect cancer cell growth, division and reproduction. Regardless of the route of administration, chemotherapy drugs are introduced into the blood stream, so that chemotherapy can cause various degree of damage to other normal organs and tissues while killing cancer cells, further causing a series of serious adverse effects/toxicity.

Hair loss is an obvious side effect of chemotherapy. The incidence of chemotherapy-induced hair loss is as high as 65% in patients receiving chemotherapy and in some is even up to 80–100% in patients receiving specific agents, such as doxorubicin and docetaxel [1–3]. Although hair loss itself does not cause damage to the body and threaten life, it can induce persistent negative emotions such as anxiety, depression and negative evaluation of self-image, which in turn reduces quality of life [4]. The hair loss caused by chemotherapy is usually reversible; however, in most cases, the color of the new hair is grayish or different from the previous color, and the hair texture also shows some changes, such as being rougher, slower growing and sparser [5, 6]. Besides, contemporary social media and excessive attention to appearance have put more pressure on patients, with 8% of patients saying that they refuse chemotherapy because of fear of alopecia [7]. Even some female patients said that having no hair is more difficult to tolerate than mastectomy [8].

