YH0618, a medicinal and edible compound prescription, is developed based on the “homology of medicine and food,” theory ancient prescription, and long clinical practice. Our previous animal studies have shown that YH0618 decoction did not interfere with the anti-tumor effects of chemotherapy drugs [12]. Additionally, a randomized clinical trial also showed that YH0618 significantly accelerated hair regrowth and reduced thumbnail pigmentation in cancer patients who have completed chemotherapy (data was not showed, but the protocol was published in [13]). Therefore, this study will further explore the efficacy of YH0618 granule on chemotherapy-induced hair loss in patients with breast cancer by a randomized, double-blind, multi-center clinical trial. YH0618 consists of five medicinal and edible foods (black soybean and liquorice, etc.) which are recommended by clinicians for cancer patients and all components have a history of safe use in other foods. Besides, each of the components possesses a distinct pharmacological profile, including removing free radicals in the body, regulating the immune system, preventing cancer, detoxifying and enhancing the sense of taste [14–16]. Black soybean and liquorice, as the main essential ingredients, have been used for detoxification for millennia in China. Based on the theory of the “Essence of the kidney is reflected on the hair” in traditional Chinese Medicine, the color, texture and growth of hair is believed to be closely related to the kidney. However, there is no in-depth research on the relationship between kidney and hair, and no research is combined with the comprehensive evaluation of renal function from the aspects of both Chinese and western medicine to explore the mechanism of chemotherapy-induced hair loss. The kidney is an important detoxification organ of the human body and helps to filter out toxins in the blood and other waste through urine. Chemotherapy drugs may not cause renal organic lesions, but they “consume” kidney essence and kidney *qi*, which breaks the balance of the body. Therefore, we believe that chemotherapy agents not only directly produce toxic effects on hair-follicle cells, but also deplete *qi*, blood and body fluids, especially kidney essence and kidney *qi*, and breaks the balance of *yin* and *yang* of the human body, which leads to the obstruction of microcirculation and the decline of immune function, further resulting in nutritional disorders of hair follicles and hair loss. Thus, the study will also elucidate the mechanism of YH0618 granule on reducing hair loss from the aspect of kidney deficiency or renal dysfunction. The hypothesis of the study is that YH0618 granules could delay chemotherapy-induced hair loss by improving kidney deficiency and renal dysfunction.

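### The 80% power rests on grade < II rates from patients who had completed chemotherapy, and nothing links them to patients graded before cycle 5

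*Protocol article*

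**What the plan says.** All planning inputs are in the protocol article under Estimation of sample size.

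- Treated arm: "YH0618 could cause the incidence of hair loss grade < II to reach 50% for patients who have completed chemotherapy".
- Difference: "the difference between the incidence of hair loss grade < II in YH0618 group and the control group was 15" per cent. With 50% under YH0618, this puts control at 35%.
- Test and error rates: "the difference in proportion between the two groups will be measured by a Z test", and "To achieve a two-sided, type-I error alpha = 0.05 and power: (1 − beta) = 80" per cent.
- Result: "the minimal number of subject need in each group is 85", then "We estimated a 20% attrition rate at the end of follow-up; hence, a sample size of at least 107 in each group (214 in total").

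The Background describes the earlier randomized trial of the product as showing that "YH0618 significantly accelerated hair regrowth and reduced thumbnail pigmentation in cancer patients who have completed chemotherapy". It adds that the data are not shown.

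The present trial has a different setting. Under Subjects, patients are receiving their first chemotherapy, with a taxane, an anthracycline or both, for at least six three-week cycles. Under Intervention and control condition, study treatment runs over cycles 1 to 4. Under Statistical analysis, the primary efficacy comparison is of hair-loss grade before cycle 5. The hypothesis at the end of the Background is that the granules delay hair loss.

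**The concern.** The planning rates and the trial endpoint describe different situations. In the source patients chemotherapy was over, and the only hair effect that the Background reports for them is faster regrowth. In this trial patients are still being treated when they are graded, and the product is meant to prevent or delay loss. The share of patients below grade II, and the effect of the product on that share, could differ in either direction between the two settings. The sample-size section goes straight from the earlier results to the Z test without addressing this.

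The Background also gives a reason to doubt 35% as an on-treatment control rate. It cites hair loss in 65% of chemotherapy patients, and "in some is even up to 80–100% in patients receiving specific agents, such as doxorubicin and docetaxel". Those two drugs belong to the classes required for entry, and scalp cooling is prohibited during the trial.

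The power statement governs how a null result is read, and it bears on the futility look described under Statistical analysis. If 80% is quoted for an endpoint to which it does not apply, a non-significant result will be taken as stronger evidence of no effect than it is.

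**Working it through.** **Inputs.** YH0618 50%, control 35% (50 − 15), two-sided alpha 0.05, power 80%, Z test, 85 per arm and 20% attrition, all from Estimation of sample size. Allocation 1:1, from Study design.

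**1. The protocol's own figure.** For a pooled two-sample Z test,

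n per arm = [z₀.₉₇₅ √(2p̄(1 − p̄)) + z₀.₈₀ √(p₁(1 − p₁) + p₂(1 − p₂))]² / (p₁ − p₂)²

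With p₁ = 0.50, p₂ = 0.35 and p̄ = 0.425:

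- 1.960 × √0.48875 = 1.370
- 0.8416 × √(0.25 + 0.2275) = 0.582
- (1.370 + 0.582)² / 0.0225 = 3.81 / 0.0225 = 169.3, so 170 per arm.

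The stated 85 is not reproduced. It does come out of a one-sample formula (50% against 35%), and it is also half of 170. The attrition step does reproduce: 85 / 0.80 = 106.25, so 107. This arithmetic error is separate from the present point, but it sets the baseline. Exact enumeration of the Z test at 85 per arm gives 52% power for 35% against 50% (normal approximation 51%; about 46% with the Fisher's exact test named under Statistical analysis).

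**2. The two settings side by side.**

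| | Source of planning rates | This trial |
|---|---|---|
| Patients | chemotherapy completed | first chemotherapy, graded before cycle 5 of at least six |
| Effect described | faster regrowth | delay of loss |
| Rate of grade < II | 50%, and 35% in control | not given |

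**3. Power under assumed on-treatment rates.** The article gives no rate of grade < II before cycle 5, so the control rates of 5, 10 and 20% below are assumptions. Two ways of carrying the effect over are shown: a fixed 15-point gap, and the planned odds ratio (0.50/0.50) / (0.35/0.65) = 1.86. For example, with control at 10% the odds are 0.111; 0.111 × 1.86 = 0.206, which is a treated rate of 17.1%. Power is by exact enumeration at 85 per arm. The detectable difference is solved from the pooled formula above.

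| Control rate | 15-point gap: treated rate | Power | Odds ratio 1.86: treated rate | Power | Difference detectable with 80% power |
|---|---|---|---|---|---|
| 5% | 20% | 87% | 8.9% | 16% | 13.8 points |
| 10% | 25% | 75% | 17.1% | 27% | 16.5 points |
| 20% | 35% | 60% | 31.7% | 42% | 19.5 points |
| 35% (protocol) | 50% | 52% | 50% | 52% | 21.3 points |

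Compared with the 52% baseline, lower control rates raise power if the absolute gap carries over and reduce it if the odds ratio does.

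**The case against.** Borrowing from the nearest available trial of the same product, and saying so, is ordinary practice. Four further points deserve weight.

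- **The Background incidence does not contradict 35%.** A reader might infer that 80–100% hair loss rules out a 35% control rate of grade < II. It does not. The incidence is given without a grade, while the WHO grading table makes grade I minor hair loss. A patient with minor loss therefore counts both as having hair loss and as below grade II. The upper range also applies only to certain agents, and the general figure is 65%. This stands: the incidence makes 35% uncertain and no more.
- **Regrowth is an inference.** The sample-size section does not say that grade < II in the earlier trial reflected regrowth. That reading joins it to the Background, and neither the timing of grading nor the grade at entry is shown. This stands too, although completed chemotherapy as the source is explicit.
- **No loss of power from the mismatch is shown.** A reader might infer that the change of population is what leaves the trial underpowered. The range of 16 to 87% includes 80%, and every fixed-gap row lies above the 52% baseline. At a correctly computed 170 per arm, the fixed 15-point gap would give 99, 96 and 88% at control rates of 5, 10 and 20%; the constant odds ratio would give 29, 49 and 70%. This stands: the direction is open.
- **The odds-ratio rows are a choice.** The protocol plans on an absolute difference. That is fair, but the article offers no reason why 15 points should carry over either.

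None of this supplies the missing link between the two settings.

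**Conclusion.** The concern holds in a limited form. The stated 80% power is supported neither for the comparison before cycle 5 nor, at 85 per arm, for the rates on which it is built, where power is about 52%. The first defect remains even if the second is corrected: a sound calculation for 35% against 50% would still use rates from patients in another phase of care.

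The size of the effect on power cannot be pinned down from the article. Over control rates of 5 to 20%, power runs from 60 to 87% with a fixed 15-point gap and from 16 to 42% with a fixed odds ratio. These ranges rest on assumed control rates, 85 evaluable patients per arm and the Z test. The article supports neither a claim that 35% is impossible on treatment nor a claim that the mismatch by itself lowers power.

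**What to change.** Revise the paragraph under Estimation of sample size as follows.

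1. Stop presenting the completed-chemotherapy result as the basis for 80% power.
2. Use rates of grade < II before cycle 5 under taxane or anthracycline chemotherapy. If none are available, label the control rate and the difference as assumptions.
3. Restate the power at 85 evaluable per arm, including about 52% for 35% against 50%.
4. Give the difference detectable with 80% power at control rates of 5, 10, 20 and 35%: 13.8, 16.5, 19.5 and 21.3 points.

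The cost is a rewritten paragraph and a less favourable stated power. The restatement needs no extra patients. Enlarging the trial to reach 80% would be a separate decision for the sponsor.

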### Statistical analysis

All analyses will be performed based on intention-to-treat principles, any missing data in the follow-up visits will be imputed using multiple imputation. Descriptive analyses as means and standard deviations (SDs) will be used to describe the demographics and clinical characteristics of the participants. The primary efficacy analysis compared the hair-loss grading between YH0618 granule and control before the fifth chemotherapy using Fisher’s exact test. The changes of hair diameter between the two groups after four cycles of chemotherapy will be compared by an independent samples *t* test. A multivariable logistic regression model will be used to explore the treatment effect. Potential confounding variables will be identified as those that differ among treatment groups at baseline and are significantly associated with outcomes. Changes from baseline to the final assessment in quality of life assessed by the FACT-B and objective indicators in the blood will be compared using Wilcoxon rank sum tests. Unless otherwise specified, two-sided statistical tests will be used and the significance level will be set at *p* < 0.05.

In this trial, an interim analysis will be performed when approximately two thirds of the planned observations are enrolled. The results are analyzed by the statistician and only DSMB members have access to the results to test for futility, safety and efficacy of the trial. A predefined stopping rule will be applied to the data to determine whether it is futile to continue enrollment.

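### The sample size is about half of what its own inputs require: 85 per group gives roughly 50% power for 50% versus 35%, not the stated 80%

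*Protocol article*

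**What the plan says.** All of the inputs stand in one paragraph of the protocol article, Estimation of sample size:

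- Rate on YH0618: "YH0618 could cause the incidence of hair loss grade < II to reach 50% for patients who have completed chemotherapy".
- Effect: the difference from control in the same proportion is given as 15%.
- Test: "the difference in proportion between the two groups will be measured by a Z test".
- Error rates: two-sided alpha 0.05 and 80% power.
- Result: "the minimal number of subject need in each group is 85", raised for 20% attrition to 107 per group, 214 in total.

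The Study design section repeats the 214 and gives 1:1 allocation. The Statistical analysis section names a different test from the one used for sizing: "The primary efficacy analysis compared the hair-loss grading between YH0618 granule and control before the fifth chemotherapy using" Fisher's exact test. The same section specifies intention-to-treat analysis with multiple imputation of missing follow-up data.

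**The concern.** Near 50%, a two-group comparison of proportions with a 15-point difference is known to need well over 100 patients per group for 80% power. A figure of 85 is too small on sight. If it is wrong, the trial does not have the power it declares. A real effect of the planned size would then be missed far more often than the one time in five that 80% power implies, and a non-significant result could be taken as evidence of no effect. Ethics committees and the DSMB, which is to look at futility at an interim analysis, would also be working from a wrong statement of what the trial can detect.

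Two further features of the plan bear on the figure. The analysis test (Fisher) is more conservative than the sizing test (Z). The planning rates come from patients who had finished chemotherapy, whereas this trial treats patients during it. For patients receiving chemotherapy, the Background says that the incidence of hair loss "is even up to 80–100% in patients receiving specific agents, such as doxorubicin and docetaxel".

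**Working it through.** **Inputs** (Estimation of sample size; allocation from Study design): p1 = 0.50, difference 0.15, so p2 = 0.35; two-sided alpha 0.05, z = 1.96; power 80%, z = 0.8416; equal groups. The control rate of 35% is inferred from the 50% and the 15-point difference. A control rate of 65% gives the same n by symmetry.

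**Required n per group**

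- Unpooled variance: (1.96 + 0.8416)² × (0.50×0.50 + 0.35×0.65) / 0.15² = 7.849 × 0.4775 / 0.0225 = 166.6, so **167**.
- Pooled variance, mean rate 0.425: [1.96 × √(2×0.425×0.575) + 0.8416 × √0.4775]² / 0.0225 = [1.370 + 0.582]² / 0.0225 = 169.3, so **170**.
- Arcsine: 169.1, so 170. With continuity correction: 182.4, so 183.

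**Attempts to reproduce 85**

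| Reading | n per group |
|---|---|
| One-sided, unpooled | 132 |
| One-sided, pooled | 134 |
| 15% as a relative difference (50% vs 42.5%) | 693 |
| Control rate of 15% (50% vs 15%) | 27 |
| One-sample test of a fixed 50% against 35% | 84.8, so 85 (single group) |

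No two-group reading gives 85. The figure equals 170/2. It also equals the one-sample result: [1.96×0.5 + 0.8416×√0.2275]² / 0.0225 = 84.8. Either slip could be the source, and the article does not say which. Neither is valid for two groups of 85.

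**Attrition step.** 85/0.8 = 106.25, so 107 per group and 214 in total. This step reproduces, so the error lies in the 85 alone. The same step from the correct figures gives 167/0.8 = 208.75, so 209, and 170/0.8 = 212.5, so 213 per group (418 to 426 in total).

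**Power actually available for 50% vs 35%**

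Normal approximation at n = 85: (0.15×√85 − 1.370) / 0.691 = 0.018, which corresponds to 50.7%. At n = 107: (0.15×√107 − 1.370) / 0.691 = 0.262, or 60.4%. Exact enumeration over both binomial distributions gives:

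| n per group | Z test | Fisher's exact test (2×2, split at grade II) |
|---|---|---|
| 85 | 51.7% | 45.5% |
| 107 | 59.4% | 54.1% |
| 170 | 80.9% | 77.8% |

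**Detectable difference at 80% power** (pooled Z, one group at 50%): 50% vs 29% needs 84 per group, so 85 supports about 21 points. 50% vs 31% needs 104 and 50% vs 31.5% needs 110, so 107 supports about 19 points.

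**The case against.** The strongest counter-argument is that the 35% control rate may not apply. The planning rates come from patients after chemotherapy. If far fewer control patients stay below grade II during treatment, the same 15-point difference needs fewer patients: 76 per group for 5% vs 20%, 100 for 10% vs 25%, 138 for 20% vs 35%. At the lowest of these rates, 85 per group would reach 80% power. That arithmetic is right, and it means that the change of population does not by itself make the shortfall worse. It does not validate the 85, because the plan uses none of these rates and gives no evidence that a 15-point difference would hold at them. The 80–100% in the Background also cannot be turned into a planning rate. It carries no grade, while the sizing endpoint counts grade I (minor loss) as success.

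Other points deserve weight:

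- **Denominator.** With intention-to-treat and multiple imputation, all 107 per group enter the analysis, so 85 is the less favourable basis. Z-test power then lies between about 52% and 59%, depending on how much information imputation recovers. It is still far from 80%.
- **Fisher figures.** They assume a split at grade II, matching the sizing endpoint. The Statistical analysis section speaks of comparing the grading and does not state the split. If all grades are compared, the Fisher powers above do not apply. The Z-test result is unaffected.
- **Time-to-event outcome.** The primary outcome is worded as the time of reaching grade II. But the sample size paragraph is explicitly a calculation on proportions, and no hazard ratio or event count is offered in support of 85.
- **Unseen documents.** A fuller protocol or analysis plan may exist. The point does not rest on missing detail, because the printed inputs and the printed result disagree.

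**Conclusion.** The concern holds. The stated 85 per group is about half of the 167 to 170 that the plan's own inputs require, and the claimed 80% power is really about 52% for the Z test at 85 evaluable per group. It is about 45% with Fisher's exact test on a split at grade II, and it reaches only 54% to 59% if all 107 per group contribute fully. The conclusion depends only on the printed inputs (50%, 15 points absolute, two-sided 0.05, 80%, equal groups). It does not depend on the direction of the difference or the variance formula, and even a one-sided test would need at least 132 per group. Which slip produced the 85 is unknown and does not matter. The source of the planning rates is a separate, secondary weakness whose effect on power could go either way.

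**What to change.** Rewrite the Estimation of sample size paragraph in one of two ways:

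1. **Keep 214.** State that 85 evaluable per group gives about 50% power for 50% vs 35% (about 45% with Fisher's test split at grade II), or that 80% power holds only for about 21 points. The second wording needs a reason to expect so large an effect, because the only estimate in the article is 15 points. This costs one paragraph and no patients, but the stated power becomes less favourable and the trial remains underpowered for its own planning difference.
2. **Keep 80% power for 15 points.** Plan 167 to 170 evaluable per group, or 209 to 213 after 20% attrition (up to 426 in total, roughly double). If Fisher's test stays, 170 falls slightly short (77.8%); the continuity-corrected 183, or 183/0.8 = 228.75, so 229 after attrition, is the closer guide.

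In either case, size on the test that will be used, state the split at grade II if that is meant, and correct the total wherever 214 appears if it changes. It would also help to replace the post-chemotherapy rates with a control rate observed during chemotherapy and to show power over a range, for example 5% to 35% of controls below grade II. That range is an assumption; the article gives no such rate.

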### Randomization and blinding

Each subject will obtain an unique number after completing written consent. A computer-blocked random number sequence with a block size of four will be generated centrally by a statistician not involving in this study. As YH0618 granule and placebo show the same appearance, a double-blind model will be adopted. Therefore, the randomization sequence and different groups will be kept hidden from subjects, practitioners, data collectors and statisticians.

